#### Cost analysis

The process of care is distinguished into three cost stages (antenatal stage, delivery/childbirth, postnatal stage) and three cost categories (direct medical costs [all costs in the health care sector], direct non-medical costs [costs outside the health care sector that are affected by health status or health care] and indirect costs [costs of sick leave]). For each stage and each cost category, costs are measured as the volumes of resources used multiplied with appropriate valuations (cost-per-unit estimates, fees, national reference prices).

Cost volumes in the antenatal stage consist of direct medical costs (e.g. hospital care, outpatient visits, administration of 17OHPC progesterone injections). Direct non-medical and indirect costs in that stage may occur if role patterns or household routines shift.

Costs during childbirth are dominated by the course of childbirth and type of delivery. Cost volumes in the postnatal stage consist of hospital-based maternal care (hospitalization etc.), neonatal care (admission to NICU/medium care or maternity ward, related diagnostic care and treatment, outpatient visits) and primary care. If neonatal health is suboptimal, further direct medical, direct non-medical and indirect costs may occur. Hence, for these infants, resource use of infants and/or parents is measured during 12 months after childbirth.

Volumes of health care resource use are measured prospectively alongside the clinical study in all participating centres as part of the CRF.

Valuations of direct medical resources are estimated as cost per unit estimates comprising "true economic" costs, i.e. including shares of fixed costs and hospital overheads. Costs per units are estimated for at least teaching and one non-teaching hospital. An analysis based on reimbursement fees is added. Direct medical volumes outside the hospital and direct non-medical volumes are valued using national reference prices [17]. Indirect costs are quantified but remain unvalued. Study-specific costs are excluded from analysis.

### Statistical issues

#### Sample size

The sample size is calculated based on the primary outcome 'bad neonatal outcome'. In the control group, 'bad neonatal outcome' is expected in 7.2% of the children (1.8%*77% + 5.4%*35% + 7.2%*12% + 35.6%*8% + 50%*.5% = 7.2%). In this calculation, the first rate represents the probability that a patient delivers at that gestational age, whereas the second rate represents the probability of 'bad neonatal outcome' at that particular gestational age. In case of treatment, 'bad neonatal outcome' is then expected in 3.9% of the children (0.9%*77% + 2.7%*35% + 3.6%*12% + 17.8%*8% + 75%*.5% = 3.9%).

Because the outcomes in children from multiple pregnancies are to a certain extent non-independent, we adjusted our sample size assuming a correlation of 0.6 for composite neonatal morbidity between two children born from the same pregnancy [18]. Using a two-sided test with an alpha of 0.05 and a power of 0.80 we need 330 women in the control group and 330 in the intervention group.

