**Methods/Design:**

We aim to investigate the hypothesis that 17OHPC will reduce the incidence of the composite neonatal morbidity of neonates by reducing the early preterm birth rate in multiple pregnancies. Women with a multiple pregnancy at a gestational age between 15 and 20 weeks of gestation will be entered in a placebo-controlled, double blinded randomised study comparing weekly 250 mg 17OHPC intramuscular injections from 16–20 weeks up to 36 weeks of gestation versus placebo. At study entry, cervical length will be measured. The primary outcome is composite bad neonatal condition (perinatal death or severe morbidity). Secondary outcome measures are time to delivery, preterm birth rate before 32 and 37 weeks, days of admission in neonatal intensive care unit, maternal morbidity, maternal admission days for preterm labour and costs. We need to include 660 women to indicate a reduction in bad neonatal outcome from 15% to 8%. Analysis will be by intention to treat. We will also analyse whether the treatment effect is dependent on cervical length.

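### 330 women per group give about 55% power, not 80%, for 7.2% versus 3.9% of children with a sibling correlation of 0.6

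*Protocol article*

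**What the plan says.** All the inputs stand in the protocol article, under Statistical issues, Sample size:

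- Control rate: "In the control group, 'bad neonatal outcome' is expected in 7.2% of the children".
- Treatment rate: "In case of treatment, 'bad neonatal outcome' is then expected in 3.9% of the children".
- Clustering: "we adjusted our sample size assuming a correlation of 0.6 for composite neonatal morbidity between two children born from the same pregnancy".
- Error rates and result: "Using a two-sided test with an alpha of 0.05 and a power of 0.80 we need 330 women in the control group", and the same number in the intervention group.

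The Data analysis section says that dependence between children of one pregnancy will be handled by a cluster analysis, so the adjustment matches the planned test. Randomisation is 1:1 (Procedures, recruitment, randomisation and collection of baseline data).

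The Methods/Design part of the abstract justifies the same total with different rates: "We need to include 660 women to indicate a reduction in bad neonatal outcome from 15% to 8" per cent.

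**The concern.** The article gives every input and the result side by side, so the result can be checked, and it does not follow from the inputs. A fall from 7.2% to 3.9% is a small absolute difference in an uncommon event, and a sibling correlation of 0.6 removes much of the information from the second child. A figure of 330 women per group looks too small on both counts.

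The power of the primary comparison is at stake. If it is nearer 55% than 80%, a non-significant result is almost as likely as a significant one even when the drug works exactly as planned. Readers who believe the trial had 80% power could then take such a result as stronger evidence against benefit than it is.

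**Working it through.** **Inputs.** p1 = 0.072, p2 = 0.039, two-sided alpha 0.05 (z = 1.960), power 0.80 (z = 0.842), correlation 0.6, equal groups, 330 women per group. One assumption is added: every pregnancy has two children. Higher-order multiples are eligible, but their share is not given.

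**1. The plan's rates reproduce.**
- Control: 1.8%×77% + 5.4%×35% + 7.2%×12% + 35.6%×8% + 50%×0.5% = 7.238%
- Treatment: 0.9%×77% + 2.7%×35% + 3.6%×12% + 17.8%×8% + 75%×0.5% = 3.869%

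**2. Children per group if all were independent.** With pooled variance and p̄ = 0.0555:

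n = [1.960·√(2p̄(1−p̄)) + 0.842·√(p1(1−p1) + p2(1−p2))]² / (p1−p2)²

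= (0.6346 + 0.2718)² / 0.033² = 0.8216 / 0.001089 = 754.4, so 755 children, or 378 women with twins.

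With the unrounded rates n = 724.2, so 725 children, or 363 women. Both exceed 330.

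**3. Adding the correlation.** Design effect = 1 + (2−1)×0.6 = 1.6.
- Rounded rates: 754.4 × 1.6 / 2 = 603.6, so 604 women per group (1,208 in total)
- Unrounded rates: 724.2 × 1.6 / 2 = 579.4, so 580 women per group (1,160 in total)

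**4. Power at the stated size.** 330 women are 660 children per group. The effective number is 660 / 1.6 = 412.5.

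z = [(p1−p2)·√n − 1.960·√(2p̄(1−p̄))] / √(p1(1−p1) + p2(1−p2))

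= (0.033 × 20.31 − 0.6346) / 0.3229 = 0.110, which is 54.4% power.

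| Correlation | Power, rounded rates | Power, unrounded rates |
|---|---|---|
| 0 | 74.5% | 76.2% |
| 0.6 | 54.4% | 56.1% |

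To arrive at 330 women the design effect would have to be 660 / 754.4 = 0.87 (0.91 unrounded), which is a negative correlation of about −0.13 (−0.09).

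**5. Does the choice of method matter?** Power at 330 women per group, two-sided, correlation 0.6, rounded rates unless stated:

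| Variant | Power |
|---|---|
| Unpooled variance | 54.6% |
| Arcsine | 55.3% |
| Log relative risk | 52.9% |
| Simulated correlated pairs (40,000 runs), difference | 55.0% |
| Simulated correlated pairs, log relative risk | 53.5% |
| Mean of 2.2 children per pregnancy (assumption) | 55.3% (57.0% unrounded) |
| Pregnancy with at least one affected child | 58.1% |

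For the last row, the share of pregnancies affected is 2p − [p² + 0.6p(1−p)], which gives 9.9% versus 5.4%. That analysis would need 553 women per group. A one-sided test, which the plan does not use, gives 66.5% with the 1.6 design effect.

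**6. Effect detectable with 80% power.** With 412.5 effective children per group and a 7.2% control rate, the treatment rate must fall to about 2.9%. That is a relative risk of 0.0293 / 0.072 = 0.41, against the planned 0.039 / 0.072 = 0.54.

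**7. The abstract's contrast.** 15% versus 8%, with the woman as the unit and no clustering, needs 325 per group; 330 give 80.6% power.

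**The case against.** The strongest reply is that 660 is not an error at all but was sized on the abstract's 15% versus 8%, which does return about 330 women per group. That is a likely origin of the number, though the article does not show how it was reached. It does not rescue the sample size section, which gives different rates, counts children and claims an adjustment for correlation. Nor are the abstract's rates the same assumption expressed per woman. In twins, the share of pregnancies with an affected child cannot exceed twice the child rate, 14.4% (14.5% unrounded). Even that bound requires that both twins are never affected, the opposite of a correlation of 0.6. What stands is that the defect is also a contradiction between abstract and main text on rates and unit, so the two must be reconciled together.

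Three smaller points have some force. Higher-order multiples and other test variants move the power by a few points, so 54% to 56% should be read as about 53% to 58%. Relative risks with 95% confidence intervals are already planned, which gives some protection when a null result is read, and nothing in the article says that such a result would be over-interpreted. A fall to 2.9% has no support in the article as a target, because the treatment rate of 3.9% already assumes that the probability of delivery in each of the earlier gestational-age strata is halved. None of these brings the power near 80%.

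**Conclusion.** The concern holds. On the plan's own inputs, 330 women per group give about 54% to 56% power for the primary comparison, roughly 25 percentage points below the stated 80%. The number needed for 80% is 580 to 604 women per group. The result rests on twins throughout and a child-level comparison; every two-sided variant tried with correlation 0.6 stays between about 53% and 58%.

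The conclusion that 330 does not follow from the stated inputs is firmer still. It is below the requirement at zero correlation, and a positive correlation can only raise that requirement. A headline design claim is materially wrong and must be corrected.

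**What to change.** Correct the sample size paragraph so that size, rates, correlation and power agree. If 660 women are kept, wording such as this would serve:

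> With 330 women (about 660 children) per group, 7.2% versus 3.9% of children affected, a within-pregnancy correlation of 0.6 and a two-sided alpha of 0.05, power is about 55%. Power of 80% is available for a reduction to about 2.9%.

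The second sentence describes what the design can detect; it should not be offered as a reason to expect so large an effect. State that the calculation assumes two children per pregnancy.

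In the same revision, align the abstract. Either replace 15% versus 8% by the child-level rates and the corrected power, or state explicitly that the trial was sized per woman, with the source of those rates and their relation to the child-level figures. Say also that a non-significant result will be interpreted from the confidence interval already planned, without appeal to 80% power.

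The cost is rewording in two places and a less favourable stated power. No extra patients are required. If the sponsor prefers to have 80% power at the stated rates, the price is a total of about 1,160 to 1,210 women instead of 660.

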#### Data analysis

Data will initially be analysed according to the intention to treat method. The main outcome variable, 'bad neonatal outcome', will be assessed by calculating rates in the two groups, relative risks and 95% confidence intervals as well as numbers needed to treat. To evaluate the potential of each of the strategies, we will also perform a par protocol analysis, taking into account only those cases that were treated according to protocol.

Time to delivery will be evaluated by Kaplan-Meier estimates, with account for different durations of gestation at entry, and will be tested with the log rank test. The other secondary outcome measures will be approached similarly to the primary outcome measure. The analysis will be stratified for chorionicity, number of multiples and parity. Furthermore, we will take account of non-independence between children born from the same pregnancy using cluster analysis.

#### Interim analysis

An interim analysis will be performed after the inclusion of 300 women. This analysis will be done by an independent data and safety monitoring committee that will not be aware of the allocation of treatment or placebo when they judge data on effectiveness. In case of severe side-effects, the safety monitoring committee can order to disclose the label of patients with such side effects.

### Ethical considerations

This study has been approved by the ethics committee of the Academic Medical Centre Amsterdam (Ref. No. MEC 05/102) and by the boards of management of all participating hospitals.

## Discussion

In the past, many strategies have been applied to prevent preterm birth in multiple pregnancies, such as bed rest, uterine activity monitoring, prophylactic tocolysis and primary cerclage. However, none of these strategies have been proven to be effective.

Whilst the aetiology of spontaneous preterm birth is multifactorial in both singleton and multiple pregnancies, prophylactic administration of progesterone has recently been shown to reduce preterm birth in women with a singleton pregnancy and a previous preterm delivery. From that perspective, and taking into account the major medical and social implications of preterm birth, research has to be done into the possible beneficial effects of progesterone in multiple pregnancies.

Simultaneously with the AMPHIA-trial, a number of other study groups in different countries have set up trials to investigate the effectiveness of progesterone in preventing preterm birth in multiple pregnancies. These are two trials in the United States, one in Canada, one in Scotland, one in Lebanon and one in Denmark [19-24]. Some of these trials use intramuscular injection, analogously to this trial, whilst others use vaginal application. If the outcome data of these studies are pooled, a more conclusive statement can be made on this matter.

## Abbreviations

17OHPC – 17-alphahydroxyprogesterone caproate

NICU – Neonatal Intensive Care Unit
